#### Cost classification

The AD-associated costs are defined as direct medical costs, direct non-medical costs, and indirect costs (Table 1).

**Table 1 Tab1:** Classification of AD-associated costs

AD-associated costs	Subgroup costs
Direct medical cost	outpatient
	hospitalisation
	out-of-pocket
Direct non-medical cost	transportation, accommodation, and meals
	nourishment
	healthcare equipment
	formal care
Indirect cost	informal care
	intangible cost

#### Direct medical costs

The direct medical costs include outpatient costs, hospitalisation costs, and out-of-pocket expenses for healthcare medications. Outpatient costs include the reason for the visit (due to AD, AD-related symptoms, or comorbidities), the number of outpatient visits in the past 3 months, and the cost of the last clinic visit in the same 3-months period. The cost of clinic visits includes registration (general physicians or specialists), diagnostic procedures (e.g., consultation, scale evaluation), imaging (e.g., CT, MRI, SPECT, and PET), laboratory tests, medication, and non-drug treatment (such as rehabilitation treatment). The outpatient medication costs are divided into three categories: anti-dementia drugs, medications for the treatment of AD-related symptoms (e.g., sleep disorders, psychiatric symptoms, and gastrointestinal symptoms caused by medications), and the treatment of comorbidities. For anti-dementia drugs the specific medications used and their corresponding costs are also investigated. For comorbidity-associated costs, the types of comorbidity and the associated costs are recorded. Investigations into the cost of hospitalisation included the reason for hospitalisation (AD, AD-related symptoms, or comorbidities), how many times a patient was hospitalised in the past 12 months, and expenditures on the last hospitalisation within the past 12 months. The hospitalisation expenditure includes the cost of the ward bed, formal care, examinations, laboratory tests, treatment (such as rehabilitation, massage, and others), and medications. The term “self-bought medications” means that the patient or their caregivers purchased the medications outside the hospital (out-of-pocket spending). Questions include how many times medications were purchased in the past month and the total expenditure during the same period. The above data also include information regarding the patients’ payment method (including medical insurance for urban workers or town residents, rural cooperative medical insurance, commercial insurance and self-funded) and any out-of-pocket expenses.

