### Distribution of investigation sites and inclusion criteria

This study covered 30 provincial, municipal, and autonomous regions in mainland China, with the exception of Tibet, Hong Kong, and Macao. The target sites included Tier 3 hospitals, mental health centres/psychiatric hospitals, gerontology hospitals, nursing homes/gerocomiums/care facilities, and both urban and rural residences. The study sites in each region were selected randomly. However, each site must meet the following pre-specified criteria: (1) Tier 3 general hospitals, mental health centres, psychiatric hospitals or gerontology hospitals with memory clinics, dementia specialists, psychological evaluation divisions, AD-relevant diagnostic equipment (e.g., computed tomography [CT], 1.5 T or above magnetic resonance imaging [MRI]), and laboratories with the ability to examine samples that may aid in the diagnosis of AD. (2) Nursing homes/gerocomium/care facilities with dementia specialists, >100 beds, and the ability to admit patients with AD. (3) Residences with >500 residents, a residence health system (e.g., electronic health records), active resident or village committees, and staff who can assist with the study. (4) Patients who fully understand the protocol and agree to participate in the study.

The study included 81 research centres that meet the inclusion criteria (Fig. 2).

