#### Direct non-medical costs

The direct non-medical costs include the cost of transportation, accommodation, and meals when visiting a physician, the cost of nourishment and healthcare equipment in the patient’s daily life, and formal care fees. The cost of daily nourishment, such as calcium, vitamin, protein powder, and fish oil supplements, include the number of times items were purchased and the amount spent in the last 12 months. The cost of healthcare equipment refers to supplies, such as positioning watches, bracelets, and wheelchairs, used in the last 12 months. Formal care costs are defined as the cost of nursing care given by professional caregivers for patients in nursing homes/gerocomiums/care facilities or at home, including the number of hours of care and the average monthly expenses [27].

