#### Per capita annual cost of AD patients (who accepted or did not accept treatment)

The cost associated with treating dementia patients (F_1_) is divided into two groups: “outpatient costs” and “hospitalised or inpatient costs.” F_1_1_ is defined as the average annual cost in the inpatient group (average annual cost × the number of inpatients annually), and F_1_2_ is the average annual cost in the outpatient group (average annual cost × the number of outpatients annually). Patients described as not accepting treatment are those who did not select either “outpatient service costs” or “hospitalised costs” in their questionnaire. F_2_ is defined as the average annual cost per AD patient who did not accept treatment.

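### Treatment that a care home itself supplies has no direct medical cost item, and the treated/untreated rule puts residents treated only there into F2, although M2 counts patients without anti-dementia treatment

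*Protocol article*

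**What the plan says.** Eligible care homes are described under Distribution of investigation sites and inclusion criteria as "Nursing homes/gerocomium/care facilities with dementia specialists, >100 beds, and the ability to admit patients with AD". The Sample size section says dementia physicians were counted at every participating site and lists care homes among the sites. The Discussion also places care homes among the institutions that have physicians for AD.

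Table 1 and the Direct medical costs section give three direct medical items; in the words of that section, "The direct medical costs include outpatient costs, hospitalisation costs, and out-of-pocket expenses for healthcare medications":
- **Outpatient cost** is built from "the number of outpatient visits in the past 3 months, and the cost of the last clinic visit in the same 3-months period".
- **Hospitalisation cost** is built from a hospital stay: "The hospitalisation expenditure includes the cost of the ward bed, formal care, examinations, laboratory tests, treatment (such as rehabilitation, massage, and others), and medications".
- **Out-of-pocket cost** covers drugs that the patient or caregivers "purchased the medications outside the hospital (out-of-pocket spending").

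Formal care is a direct non-medical item, defined as "the cost of nursing care given by professional caregivers for patients in nursing homes/gerocomiums/care facilities or at home". Under Total cost per patient per year, the facility fee is reduced by 8% of the basic cost for ordinary living expenses. It is not otherwise split.

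For the national estimate, the Per capita annual cost section sorts patients by questionnaire response: "Patients described as not accepting treatment are those who did not select either" the outpatient or the hospitalised cost item. Their mean annual cost is F2. The section on the current number of patients defines M2 differently, as patients who do not receive anti-dementia treatment. It puts the treated share d at 10–30%. The Nationwide cost section multiplies M2 by F2.

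**The concern.** The site criteria make treatment inside the home a foreseeable situation, but the cost classification names no place for treatment that the home supplies and bills. Without a rule, one site may enter such a cost as an outpatient visit, another may leave it inside the care fee, and a third may not record it.

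The same gap reaches the treatment label. The sorting rule looks at which cost items were selected, whereas M1 and M2 are defined by anti-dementia treatment. A resident who receives anti-dementia treatment only from the home, and who selects neither item, is costed as untreated but belongs to the treated count. Self-bought medications do not count under the rule either, so a patient whose anti-dementia drugs are bought only by the family can be labelled in the same way.

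At stake are the medical/non-medical split for residents, and whether F2 is the mean cost of the group it is multiplied by.

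**Working it through.** **1. The plan's own figure.** The Sample size section gives SD 11,037 and allowable error 500. Alpha is not stated; two-sided 0.05 is assumed here. Then n = (1.96 × 11,037 / 500)² = 1,871.8, rounded up to 1,872. Allowing for 25% loss, 1,872 / 0.75 = 2,496, which agrees with about 2,500. The figure reproduces and does not depend on this point. The 500 is used below only as a yardstick, in a currency the article does not state.

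**2. Tracing treatment in the home through the cost lines.**

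| What the resident receives | Line that would hold it |
|---|---|
| Clinic visit or hospital admission | Outpatient or hospitalisation |
| Drugs bought by resident or family | Self-bought medications; a care home is not a hospital |
| Consultation by the home's specialist | Not named; could be entered as an outpatient visit |
| Therapy or drugs supplied and billed by the home | Not named |
| Nursing care in the home | Formal care (non-medical) |

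**3. Tracing the label.** A resident treated only through the unnamed rows, who selects neither the outpatient nor the hospitalised item, is assigned to F2. By the definition of M1 and M2, a resident on anti-dementia treatment belongs to M1.

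**4. Effect on the national mean.** Read F1 and F2 as per-patient means. Dividing the national total by M gives

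mean = (d/7) × F1(inpatient) + (6d/7) × F1(outpatient) + (1 − d) × F2.

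At d = 10% the weights are 1.4%, 8.6% and 90%. At d = 30% they are 4.3%, 25.7% and 70%.

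Let U be the mean recorded cost of truly untreated patients. Let w be the share of the F2 group who are residents treated only in-house, and D their recorded cost minus U. Then F2 = (1 − w) × U + w × (U + D) = U + w × D, so the F2 term shifts the mean by (1 − d) × w × D.

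The documents give neither w nor D. With w assumed:

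| w (assumed) | d = 10% | d = 30% |
|---|---|---|
| 5% | 0.045 D | 0.035 D |
| 15% | 0.135 D | 0.105 D |
| 30% | 0.27 D | 0.21 D |

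At w = 15% the shift reaches 500 when |D| is 500 / 0.135 ≈ 3,700 (d = 10%) or 500 / 0.105 ≈ 4,800 (d = 30%). This covers the F2 term only. Moving these residents into the treated group would also change F1, whose terms carry total weight d.

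**5. Sign.** Facility fees raise D, and unrecorded in-house medical cost lowers it. Truly untreated residents also bring facility fees into U. D may be positive or negative.

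**The case against.** The strongest defence is that much of the treatment in a home can be recorded. Clinic-visit cost is described by content (registration, consultation, scales, medication, non-drug treatment) and is not tied to a hospital. An in-house consultation can therefore be entered as an outpatient visit, which also makes the resident treated. Family-bought drugs fit the self-bought line. The mapping of a facility bill to a cost line may be in the case report form, operator manual or questionnaire, none of which is shown. This stands, and it confines the gap to what the home itself supplies and bills. It also means that residents with a clinic visit or admission recorded in the recall window are not mislabelled.

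A second defence is that cost absorbed in the care fee remains in the patient's total, apart from whatever the 8% deduction touches. This also stands: in that case the total changes little and mainly the medical/non-medical split moves.

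The defence does not reach the sorting rule. The article prints it in full, and it uses a criterion different from the one that defines M2. That is a conflict between two stated definitions, not detail left to another document.

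A reader might infer that every sampled home treats and tests in-house. The text does not say so. Having dementia specialists is a selection criterion, and homes, unlike hospitals, are not required to have imaging or laboratories.

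**Conclusion.** The point holds in this form. No direct medical item is assigned to consultations, therapy or drugs that the home supplies and bills. Residents treated only that way, who select neither cost item, enter F2 although M2 is meant to exclude patients on anti-dementia treatment. F2 and M2 then describe different groups in a term weighted 70–90%. That weight applies to F2 as a whole, not to the misassigned residents, whose number is unknown. The problem should be corrected, but its size and sign cannot be established from the documents. The coefficients in the working rest on assumed values of w.

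A reader might go further and put a figure on the missing cost. Taking 14% as the complement of the 86% living at home under Sensitivity analyses, with an assumed 30–70% treated in-house at an assumed 3,000–12,000 a year, gives 0.14 × 0.3 × 3,000 = 126 to 0.14 × 0.7 × 12,000 = 1,176 per patient. The documents do not support this range. The shares and costs have no source, the 14% is not stated to be a care-home share and is not a weight in the national formula, and the calculation treats every unit of cost as lost. Nor can one conclude that F2 is inflated by high-fee residents, since untreated residents properly carry facility fees too.

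**What to change.** 1. In Table 1 and the Direct medical costs section, add a line for consultations, therapy and medication supplied by the nursing home, gerocomium or care facility, annualised like the other items. Where the care fee already contains this cost, take it out of the fee so that it is counted once.
2. In the Per capita annual cost section, classify a patient as treated by receipt of anti-dementia treatment from any source, including the facility and self-bought drugs. F1 and F2 then match M1 and M2. Sorting by any medical cost would not achieve this, because it would also count treatment for comorbidities alone.
3. State where residents treated in-house fall in the 1:6 inpatient/outpatient split. That ratio comes from hospitals and does not settle it.
4. If collection is closed, use site records where they hold the information, and report a sensitivity analysis that moves these residents from the F2 group to the treated group.

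The cost is one cost line, one classification sentence, one rule for the split, and some extra data work at the care-home sites. Facility billing may not be available everywhere, because the article names medical-record and residence health systems, with interviews where needed, as its sources.

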### Data collection procedure

Electronic medical record systems are being used to identify elderly patients diagnosed with AD among outpatients (in the last 3 months), inpatients (in the last 12 months), those living in urban residences and rural residences with their families, and residents of nursing homes, gerocomiums, or care facilities. The diagnosis of AD is re-confirmed by dementia specialists before the start of the study. The intensive dementia training program conducted in national and regional centres included both theory and practice. It comprised the study methods, assessment of the scales and internationally accepted diagnostic criteria of dementia and its subtypes, neuroimaging (CT and MRI), and standard procedures for diagnosis. Investigators are contacting patients and re-confirm the accuracy of the AD diagnosis according to the inclusion and exclusion criteria. Neuroimaging and laboratory tests will be performed when necessary. New patients are also being enrolled during the study period. Face-to-face questionnaires will be administered to AD patients and their caregivers when the data and information could not be collected through electronic medical record or residence health systems. The surveys are being administered by investigators to ensure the accuracy of the diagnosis and data.

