### Measures

#### Total cost per patient per year

The total cost per patient per year is determined by adding the annual direct medical costs, direct non-medical costs, and indirect costs for each patient. When calculating the cost of the recuperation fee for patients who required nursing care in nursing homes, gerocomiums, or care facilities, 8% of the basic cost is subtracted to reflect the AD patient’s basic cost of living [30]. Two approaches are being used to estimate the monetary loss of informal caregivers. For the informal caregivers who have no stable job before taking care of the AD patients, the average labour market income reported by each research centre is being multiplied by the amount of time spent being a caregiver to obtain the monetary loss. For individuals with a stable job before taking care of the AD patient, the monetary loss is being obtained by multiplying the hourly salary before they stop working by the time spent (hours) being a caregiver. All of the costs will be converted into the average annual cost.

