#### Current total number of patients with AD in China

A model is established to estimate the total number of Chinese patients with AD in 2015 based on the literature. The total number of patients with AD is defined as M and the percentage of AD patients who received anti-dementia treatment is defined as d%. Therefore, the number of anti-dementia treated patients (M_1_) is M × d%, and the number of patients not treated for dementia (M_2_) is M × (1–d)%. Based on previous reports, the percentage of AD patients who are treated for dementia is 10–30% [31, 32]. Epidemiological studies have revealed that the number of AD patients in China aged ≥ 60 years in 1990, 2000, and 2010 was 1.93 million, 3.71 million, and 5.69 million, respectively [8, 33, 34]. A linear regression model is used to estimate the age-specific prevalence of AD in 2015 by recording the prevalence of AD among different-aged patients. By multiplying the percentage of AD among elderly individuals aged ≥ 60 years by the total national elderly population (aged ≥ 60 years) in 2015, we obtain the estimated total number of AD patients of China, which is defined as M.

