#### Nationwide cost due to AD

A pilot study is performed, which reveal that the average annual ratio of inpatients to outpatients in different hospitals is ~1:6. Hence, the number of patients who undergo treatment nationwide (M_1_) is multiplied by 1/7 or 6/7 to obtain the number of hospitalised patients with AD (M_1_1_) and the number of outpatients with AD (M_1_2_), respectively. Thus, the total national annual cost of patients who accept treatment is M_1_1_ × F_1_1_ + M_1_2_ × F_1_2_. M_2_ is defined as the number of patients who did not accept treatment, and this value is multiplied by F_2_ to obtain the total annual national cost of patients who do not accept treatment. Therefore, the total annual national cost of patients with AD is M_1_1_ x F_1_1_ + M_1_2_ x F_1_2_ + M_2_ x F_2_. To estimate the costs attributable to AD, generalised linear models (GLMs) related to coexisting conditions (stroke, diabetes, heart disease, hypertension, lung disease, cancer, arthritis, and psychiatric problems) and demographics (sex, age, educational level, marital status, and household income) are used. Moreover, we estimate the total numbers of people who will be living with AD in 2020, 2030, 2040, and 2050 to predict the total annual cost of AD in future decades. Few large-scale national surveys of the monetary cost or economic burden of AD have been conducted in China, or indeed in Asia. To remedy this lack of data, we also systematically review COI studies of AD that report annual costs per patient. This will enable estimation of the proportion of the global burden of AD costs faced by China. Furthermore, it will enable comparison of the economic burden of AD in developed and developing countries.

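### Outpatients are found through a visit in the last 3 months and their visits are counted over 3 months, so annualised visits are likely overstated for that stream and probably in F_1_2

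*Protocol article*

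**What the plan says.** Under Direct medical costs, the protocol article collects the reason for the visit, "the number of outpatient visits in the past 3 months, and the cost of the last clinic visit in the same 3-months period". The visit cost covers registration, consultation, scales, imaging, laboratory tests, drugs and non-drug treatment. Admissions are counted over 12 months, and the cost of the last one is recorded.

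Under Data collection procedure, records are used to "identify elderly patients diagnosed with AD among outpatients (in the last 3 months), inpatients (in the last 12 months"), together with "those living in urban residences and rural residences with their families, and residents of nursing homes, gerocomiums, or care facilities". It adds: "New patients are also being enrolled during the study period".

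Under Total cost per patient per year: "All of the costs will be converted into the average annual cost". No factor or formula is given.

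Under Per capita annual cost of AD patients: "Patients described as not accepting treatment are those who did not select either “outpatient service costs” or “hospitalised costs” in their questionnaire". Under Nationwide cost due to AD, the number treated "is multiplied by 1/7 or 6/7 to obtain the number of hospitalised patients with AD", with 6/7 going to the outpatients, and the outpatient mean F_1_2 is applied to them. The treated share comes from the literature: "the percentage of AD patients who are treated for dementia is 10–30" per cent.

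**The concern.** For the clinic stream, the event that brings a patient into the study is the same event that is then counted, over a window of equal length. Nobody in that stream can have zero visits in the window. A patient who attends once or twice a year is either missed or caught in a quarter with a visit, and scaling that quarter to a year credits at least four visits. The inpatient stream does not have this problem: it is identified and counted over 12 months, so no scaling is needed.

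The effect probably reaches beyond the clinic stream in one place. The only outpatient window described is 3 months, so a patient from any stream without a visit in it has no outpatient cost to report and, unless admitted, falls into the untreated group. The group behind F_1_2 is then also conditioned on a recent visit. F_1_2 feeds the national annual cost, which is a main result.

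A second weakness is that one visit's cost stands for all. If that visit was a one-off diagnostic work-up, or if the work-up came earlier, the last visit's cost misrepresents the others.

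**Working it through.** **Inputs.** From the article: 3-month identification and 3-month count for outpatients; 12 months for both in inpatients; annualisation without a stated factor; 6/7 of the treated; treated share 10–30%. Not in the article, hence assumed: scaling by 4, a visit rate L per year (2, 4 and 12 tried), Poisson visits, and identification and count windows that coincide. The article states no visit rate, cost per visit or annualised outpatient figure, so there is none of its own to reproduce. The sample size does not depend on this point.

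**Step 1, visit count.** Among patients with at least one visit in the window, the mean annualised count is 4 × (L/4)/(1 − e^(−L/4)) = L/(1 − e^(−L/4)). The true mean among patients with at least one visit in the year is L/(1 − e^(−L)).

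| L | 1 − e^(−L/4) | Annualised | True | Ratio |
|---|---|---|---|---|
| 2 | 0.3935 | 5.08 | 2.31 | 2.20 |
| 4 | 0.6321 | 6.33 | 4.07 | 1.55 |
| 12 | 0.9502 | 12.63 | 12.00 | 1.05 |

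**Step 2, other attendance patterns.** With evenly spaced visits the ratio is 1/min(1, L/4): 4 at one visit a year, 2 at two, and 1 (no bias) at four or more. If rates vary between patients as a gamma distribution with shape 1, the ratio against annual attenders is (4 + L)/(1 + L): 6/3 = 2.0, 8/5 = 1.6 and 16/13 = 1.23 at mean rates 2, 4 and 12.

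**Step 3, dilution by the other streams.** If a share f of the sample comes from the clinic stream and the rest have the same visit rate without selection, the ratio for the overall mean visit count is f/(1 − e^(−L/4)) + (1 − f). At f = 0.5 this gives 0.5 × 2.54 + 0.5 = 1.77 for L = 2, 0.5 × 1.58 + 0.5 = 1.29 for L = 4, and 1.03 for L = 12.

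**Step 4, last-visit cost.** Suppose four visits a year, one of them a work-up costing 5 times a routine visit (assumed). True annual cost is 3 + 5 = 8 routine units. Costing all four visits at the work-up price gives 20/8 = 2.5; at the routine price, 4/8 = 0.5. With the inflated count of 6.33 these become 6.33 × 5/8 = 3.96 and 6.33/8 = 0.79. If the last visit is simply a random visit, its cost adds no bias on average.

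**Step 5, reach in the national total.** 6/7 of 10–30% is 8.6–25.7% of all patients with AD.

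**Step 6, does a 12-month count suffice?** If identification stays at 3 months but visits are counted over 12, the mean is (L/4)/(1 − e^(−L/4)) + 3L/4: 1.27 + 1.5 = 2.77, 1.58 + 3 = 4.58 and 3.16 + 9 = 12.16. Against the true means the ratios are 1.20, 1.12 and 1.01. Most of the bias goes, but not all; with identification also over 12 months it is zero.

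**The case against.** The strongest reply is that much of the mechanism is inferred. The article gives no annualising formula, and such detail is commonly left to the full protocol. Drug-specific costs are also recorded, and the Discussion says electronic records determine the cost of all treatment items, so last-visit cost may not be the only input. Only one stream is selected on a clinic visit. The article does not say that the two 3-month windows coincide; with less overlap the bias shrinks. If all patients attend regularly at least every quarter, there is none. Patients without a recent visit carry no outpatient cost into F_2, which could partly offset the national total.

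Most of this limits size, not existence. A 3-month count has to be scaled to a year somehow, and no adjustment for selection on a visit is described. Dilution applies to the overall sample mean, but less to F_1_2, given how untreated patients are defined. The offset through F_2 cannot be sized: the treated share comes from the literature, so infrequent attenders classed as untreated do not reduce the number multiplied by F_1_2.

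A reader might infer that outpatient cost is overstated for every patient, that F_1_2 or the national cost is 2.2 times too high, or that each new patient's work-up is counted four times. The documents support none of these. The ratios are for visit counts, whereas annual cost also contains non-medical and indirect components. Nothing says that a new patient's last visit is the work-up; it may be a follow-up, and the error then runs downward.

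**Conclusion.** The point holds for the visit count. Annualised outpatient visits are likely overstated for patients identified through a clinic visit, and probably for the group behind F_1_2. Under scaling by 4, Poisson visits and coinciding windows, the factor is about 2.2 at 2 visits a year, 1.55 at 4 and 1.05 at 12. It falls to 1 with regular attendance at least every 3 months, and the other streams dilute it in the overall sample. No corrected cost can be computed, because the article gives neither visit rates nor costs per visit. Using the last visit's cost for all visits is a separate source of error without a fixed direction.

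**What to change.** Where electronic records exist, identify outpatients by attendance in the past 12 months, count their visits over the same 12 months and sum the actual charges. This matches the window already used for admissions, and one-off work-up costs enter once. If identification must stay at 3 months, the 12-month count still removes most of the bias, and weighting can deal with the rest. State the annualising formula for every component.

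Where only 3-month interview data exist, keep the 3-month recall, since a longer one trades coverage against recall error. Report a sensitivity analysis that weights each clinic-identified patient by the inverse of the probability of a visit in the window, given a visit in the year, with visit rates estimated from the 12-month records. The weights belong in the denominator: divide the unweighted sum of annualised costs by the sum of the weights. Weighting numerator and denominator alike would not do, because with equal rates the weights cancel. At L = 4 the weight is 1.55, and 6.33/1.55 returns the true mean of about 4.07 up to rounding.

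The cost is a longer extraction from record systems already in use, plus one added sensitivity analysis.
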